#### Primary study parameter analysis

The occurrence of death rattle with a severity of grade ≥ 2 according to the scale of Back in both groups will be compared using the Chi squared test or, if necessary (i.e., if an observed number ≤ 10 or an expected number < 5 occurs in one of the cells of the 2 × 2 table), the Fisher’s exact test, to test the statistical significance of differences.

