### Randomization

Block randomization with varying block sizes of 2–4 is applied to create a randomization list for the study medication (verum or placebo) within each center (i.e. randomization is stratified by center).

As a result, verum and placebo are equally distributed over both patients and sites.

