### Sample size calculation

For the power calculation we used data from a previous study. In a sample of 400 deaths, 39% of the patients developed a death rattle with a severity of grade ≥ 2 according to the scale of Back (personal communication). We aim to reduce the occurrence of death rattle from 39 to 19%. Given a two-sided significance level of 0.05 and 80% power, a total of 180 patients are required based on a continuity-corrected Chi-square test. Taking into account that 10% of the patients who have given informed consent are expected to drop out before the actual start of the study because of sudden death or the occurrence of exclusion criteria, 200 patients are needed in total. Turnover in the four hospice settings is high: in the first three months of 2015, 120 patients were admitted, that is about 480 per year. Based on a 40% participation rate (= 192 out of 480), recognition of the dying phase and application of the CPD in 80% of all consenting patients(= 153 of 192) and a drop out of 10% it is possible to include approximately 140 patients in a year. This means that an inclusion period of approximately 18 months is needed.

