The second issue concerns the consent procedure. We ask patients’ consent to participate in the study at their admission in the hospice, when they are still capable of understanding the information and able to decide whether they want to participate. They may withdraw at any moment after signing the informed consent form. The actual study will start at the recognition of the dying phase, at which moment most patients are not able of giving consent due to their deteriorating condition. Rees and colleagues stated that asking advanced consent seems to be an acceptable alternative procedure, allowing research in patients who are unable to give consent at the time of randomization [23]. Patients who are admitted to a hospice facility in the Netherlands typically stay there until death, which makes a strategy of advanced consent feasible.

Our third strategy involves evaluation of the views of relatives about participation of their loved one in research in the last days of life. We developed a questionnaire which will be sent to relatives three months after the death of the patient. The challenge will be to sensitively ask relatives for consent to send this questionnaire at the moment the patient is admitted to the hospice.

This study has a few limitations. One limitation is the recognition of the dying phase. Although the staff is very experienced, inter-individual variability can occur. In the training of the teams, there has been thorough attention for signals that can indicate that the dying process has started. Another limitation is that although all the strategies presented aim to ensure adequate inclusion rates, the turnover of patients in the hospices fluctuate over time.

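### Randomisation is stratified by hospice, but the primary test pools the hospices and can be moved to Fisher by a small observed count; this is harmless at the planned rates and conservative outside them

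*Protocol article*

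**What the plan says.** All references are to the protocol article.

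- **Randomization:** lists are built in small blocks within each centre, so that "randomization is stratified by center" and "verum and placebo are equally distributed over both patients and sites". Study design gives four hospices.
- **Primary study parameter analysis:** the proportions with rattle of grade 2 or more "will be compared using the Chi squared test or, if necessary", Fisher's exact test. Either of two conditions makes Fisher necessary: an observed cell of 10 or less, or an expected cell below 5. There is no hospice term. The section does not say whether the chi-squared test is continuity-corrected.
- **Secondary study parameters analysis:** time to rattle is compared by Kaplan-Meier and a log-rank test, again without hospice.
- **Sample size calculation:** the target is a fall in rattle from 39% to 19%, tested two-sided at 5% with 80% power. The conclusion is that "a total of 180 patients are required based on a continuity-corrected Chi-square test".
- **Discussion:** on recognising the dying phase, "Although the staff is very experienced, inter-individual variability can occur".

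**The concern.** Two features of the primary test deserve attention.

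**Pooling over hospices.** Allocation balanced within hospice removes differences between hospices from the treatment contrast. A pooled 2 × 2 test still counts those differences in its variance. If hospices differ in rattle rate, the standard error is too large, so the test rejects too rarely under the null and loses some power. Entry depends on staff recognising the dying phase and the outcome on nurses judging audibility, so some variation between hospices is plausible.

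**The observed-count trigger.** The chi-squared approximation depends on expected counts, which the plan's second condition already covers. The condition on observed counts protects nothing further and lets the result choose the test. It fires when one arm has few events, which is what effective prophylaxis would produce.

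What is at stake is a missed effect, not a false positive.

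**Working it through.** **Inputs.** From Sample size calculation: two-sided alpha 0.05, 80% power, 39% versus 19%, 180 patients (90 per arm at 1:1). From Study design: four hospices. Hospice-specific rates and hospice sizes are not given, so they are assumptions, shown as a range.

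**Step 1: the plan's own figure.** With mean rate 0.29:

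n = [1.96·√(2·0.29·0.71) + 0.8416·√(0.39·0.61 + 0.19·0.81)]² / 0.20² = (1.2577 + 0.5268)² / 0.04 = 79.6, so 80 per arm uncorrected.

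With continuity correction: (79.6/4)·[1 + √(1 + 4/(79.6·0.20))]² = 89.3, so 90 per arm, 180 in total. Then 180/0.90 = 200. Both stated figures reproduce.

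**Step 2: the plan's rule with similar hospices.** Exact binomial enumeration at 90 per arm, uncorrected chi-squared:

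| True rates | Fisher triggered | Rejects, plan's rule | Rejects, chi-squared always |
|---|---|---|---|
| 39% / 19% | 3.2% | 85.0% | 85.0% |
| 24.8% / 12.1% (same ratio, lower rates) | 46.7% | 57.0% | 59.8% |
| 39% / 39% (null) | 0.0% | 5.25% | 5.25% |
| 19% / 19% (null) | 6.3% | 4.3% | 4.9% |
| 15% / 15% (null) | 34% | 3.4% | 4.9% |
| 12% / 12% (null) | not tabulated | 3.2% | 5.0% |

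The trigger is free at the planned rates and bites only when events are scarcer than planned.

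**Step 3: one data set.** Take 20 versus 10 events of 90 per arm. Chi-squared = 180·(20·80 − 10·70)² / (90·90·30·150) = 4.00, p=0.0455. The smallest expected count is 30/2 = 15, far above 5. The observed 10 still forces Fisher, p=0.071. The same reversal occurs at 19 versus 9, 18 versus 8 and 16 versus 7.

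**Step 4: why pooling is conservative when hospices differ.** With equal hospices, the mean within-hospice variance is p(1−p) minus the variance of the hospice rates. For null rates of 19, 32, 46 and 59% (mean 39%), that variance is (0.20² + 0.07² + 0.07² + 0.20²)/4 = 0.0225, against 0.39·0.61 = 0.2379. The pooled standard error is then too large by √[1/(1 − 0.0225/0.2379)] = 1.05, or 5%. For 29, 36, 42 and 49% the same sum gives 0.00545 and a factor of 1.01.

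**Step 5: plan's rule against Cochran-Mantel-Haenszel (CMH).** With a_k active-arm events, t_k total events and n_k patients per arm in hospice k:

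X² = [Σ(a_k − t_k/2)]² / Σ{n_k²·t_k·(2n_k − t_k) / [(2n_k)²·(2n_k − 1)]}

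Simulation with 400,000 trials per row, near-equal hospices, and overall rates held at 39% and 19% (39% in both arms for the null):

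| Control rates across hospices (assumed) | Type I error, plan / CMH | Power, plan / CMH | Power difference |
|---|---|---|---|
| all 39% | 5.35% / 5.2% | 84.9% / 84.8% | −0.1 |
| 34–44% | 5.2% / 5.2% | 85.0% / 85.0% | 0.0 |
| 29–49% | 5.0% / 5.15% | 85.2% / 85.6% | 0.4 |
| 19–59% | 4.1% / 4.85% | 85.9% / 87.6% | 1.7 |
| 12–66% | 3.4% / 5.0% | 86.8% / 89.8% | 3.0 |

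Hospice sizes of 40, 25, 15 and 10 per arm give nearly the same figures. A separate run at 19–59% with four hospices of 45 patients gives type I error of 4.2% pooled and 5.0% CMH.

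**The case against.** The case for leaving the plan alone is substantial.

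- **The documents lean towards similar hospices.** Procedures are described as largely alike, all sites use the same care programme, staff were trained on site, and the rattle scale has physical anchors. The remark that "Although the staff is very experienced, inter-individual variability can occur" concerns individuals recognising the dying phase, not rattle rates between hospices. This stands: wide spreads are neither shown nor excluded, and moderate ones cost almost nothing.
- **There is a cushion.** The size was set for a continuity-corrected test, 180 where 160 would do uncorrected. This also stands: with overall rates at plan, power stays above 80% in every row.
- **The Fisher rule is fixed in advance and can only be conservative.** True, so there is no analyst discretion and no inflation. It still has no basis in validity, and Step 3 shows that it can decide the result.
- **Detail may sit in an analysis plan that is not shown.** For the log-rank test that is a fair reply, and stratifying it is only a matching change. The primary test and its numerical trigger, however, are fixed in the article.

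Stronger readings are tempting and are not supported.

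- A reader might infer that the trial as planned loses power and runs below 5% error. At the planned rates with similar hospices the rule has 85.0% power and 5.25% error.
- A reader might infer that pooling drags power below 80%. A simulation with hospice rates of 12–69% and a fixed odds ratio does give 74.5%. Spreading rates at a fixed odds ratio, however, raises the mean active-arm rate to about 22% and shrinks the overall difference, so CMH itself reaches only 79.0%. Only the 4.5-point gap comes from ignoring hospice.
- If the chi-squared test is meant to be continuity-corrected, error is 3.7% and power 81.1% at plan. That is the effect of the correction, not of pooling, and the Fisher switch then matters little.

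**Conclusion.** The concern holds in a conditional form. The primary test does not follow the randomisation strata, and its observed-count trigger is unnecessary.

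- **At the planned rates with little hospice variation:** no cost.
- **With hospice differences (assumed):** under 1 point of power lost up to a 29–49% spread. The loss is about 2 points at 19–59%, with type I error about 4.2% against about 5% for CMH, and about 3 points at 12–66%.
- **With event rates below plan:** at about 25% versus 12% the trigger fires in 47% of trials and power is 57.0% instead of 59.8%. Under a common rate of 12–15%, type I error is 3.2–3.4%.

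The 5.25% at plan belongs to the ordinary chi-squared test with discrete data. Neither feature criticised here raises the error rate, so a positive result would stand. The figures assume 90 per arm and an uncorrected chi-squared test. Severity is minor: this is a free improvement.

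**What to change.** 1. Make the primary test a Cochran-Mantel-Haenszel test stratified by hospice, and report a stratified risk difference with its 95% confidence interval. State whether a continuity correction is applied; the CMH figures above are without one.
2. Delete the trigger on observed counts of 10 or less. Keep only the expected-count criterion for moving to an exact test.
3. Stratify the log-rank test for time to rattle by hospice.

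The cost is analysis wording, to be settled before unblinding. Hospice is already known for every patient as the randomisation stratum, and the methods are available in the named software. If hospices turn out alike, the price is about 0.1 point of power (84.8% against 84.9%). The sample size need not change.

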#### Secondary study parameters analysis

The time until the occurrence of death rattle will be compared by means of the Kaplan-Meier method and the log-rank test. The occurrence of adverse events, i.e. urinary retention and dry mouth (yes/no) will be described and compared using the Chi squared test or, if necessary, Fisher’s exact test to assess statistical significance. Restlessness will be compared using the t-test or, if necessary, the Mann-Whitney U-test.

Quality of life during the last three days of life and quality of dying will be described and compared by means of a t-test (or Mann-Whitney U test if necessary). The qualitative descriptions of the quality of dying will be summarized. Bereavement of relatives according to the ITG and experience of relatives on the patient’s participating in a (double-blind, placebo-controlled) clinical trial will be analyzed with descriptive statistics, and compared using the Chi squared test for trends.

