### General procedure

#### Regular hospice care

In the Netherlands, patients who are admitted to a hospice facility in principle have a life expectancy of less than three months and stay there until death. Standard procedure at admission includes an interview about their symptoms, care needs and expectations, by both a doctor and a nurse.

Marking of the start of the dying phase, the last 2–5 days of life, is based on recognition of a number of signs by the nurses and doctors of the hospice: the patient is bedbound, only able to take sips of fluid, no longer able to swallow and take oral medication, and/or subcomatose.

When this state is recognized, the patient and his family are informed that death is imminent and they receive explanation about the care given in these last days and what symptoms might occur. They also receive a leaflet with written information. The recognition of the dying phase is a signal to start the Care Program for the Dying (CPD). The CPD is a digital, structured template for care in the last days and hours of life. This template defines goals of care in all four domains of palliative care (e.g. on pain, dyspnea, restlessness, nausea, death rattle, oral hygiene, needs of family on psychological/spiritual domain, needs of the patients on psychological/spiritual domain). The nursing staff evaluates these aspects of care and symptoms every four hours. They report their observations in the CPD. The observations are continued until the patient dies. The CPD is standard of care in the hospice facilities that participate in this study.

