#### Secondary outcomes

Time from the recognition of the dying phase until the occurrence of death rattle (in hours)Occurrence of adverse events, i.e. urinary retention, dry mouth and restlessnessQuality of life during the last three days of life and quality of dying, both according to the attending nurse and relativesBereavement of relativesExperience of relatives concerning the patient’s participation in a (double-blind, placebo-controlled) clinical trial

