### Data collection

Data collection starts when the dying phase starts and the CPD is implemented. Collection of patient-related information will be continued until death. All data will be collected on electronic case report forms using ALEA™, an online electronic database application as implemented by the Clinical Trial Center of the Erasmus MC Cancer institute (CTC).

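### Kaplan-Meier curves for time to death rattle will overstate the share of patients who rattle, increasingly over time, if deaths without rattle are censored

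*Protocol article*

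**What the plan says.** Under Secondary outcomes, the Protocol article lists the time in hours from recognition of the dying phase to death rattle. Its method is fixed under Secondary study parameters analysis: "The time until the occurrence of death rattle will be compared by means of the Kaplan-Meier method and the log-rank test". No rule is given for patients who die without rattle, and neither competing risks nor cumulative incidence is mentioned.

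Follow-up runs to death. Under Regular hospice care, "The observations are continued until the patient dies"; under Data collection, "Collection of patient-related information will be continued until death". The period is short: "Marking of the start of the dying phase, the last 2–5 days of life, is based on recognition of a number of signs".

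The design rates come from Sample size calculation. In the earlier series, "39% of the patients developed a death rattle with a severity of grade ≥ 2 according to the scale of Back", and the stated aim is: "We aim to reduce the occurrence of death rattle from 39 to 19" per cent. The primary outcome is the plain percentage of patients with rattle, compared by a chi-squared or Fisher's exact test.

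**The concern.** Apart from withdrawals, every patient without rattle leaves observation by dying, and a patient who has died can no longer rattle. Death is therefore a competing event, and at the design rates it is the more common first event in both arms.

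A Kaplan-Meier estimate with deaths censored treats the dead as if they could still rattle later, at the same rate as those still alive. 1-KM then describes a hypothetical population in which nobody dies before rattling. A reader is likely to take such a curve as the proportion affected by a given hour, and it would not show that. It could end well above the primary percentage for the same patients, with a wider gap between the arms than the primary result shows.

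**Working it through.** **1. The plan's own figure.** Inputs from Sample size calculation: 39% vs 19%, two-sided 0.05, 80% power, continuity-corrected chi-square. The mean rate is 0.29 and the difference 0.20.

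- Uncorrected n per arm = [1.960·√(2·0.29·0.71) + 0.842·√(0.39·0.61 + 0.19·0.81)]² / 0.20² = 79.6, so 80.
- Corrected n per arm = (79.6/4)·[1 + √(1 + 4/(79.6·0.20))]² = 89.3, so 90, which is 180 in total.
- With 10% drop-out: 180/0.90 = 200.

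Both stated totals reproduce. They concern the primary percentage and do not depend on the time-to-event method.

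**2. How often death comes first.** Control: 100 − 39 = 61%. Treated: 100 − 19 = 81%.

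**3. Closed form under constant cause-specific hazards (an assumption).** Let p be the final share with rattle and q the share whose follow-up has ended by rattle or death. The true cumulative incidence is p·q, and 1-KM is 1 − (1 − q)^p. At q = 0.9:

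- Control: true 0.39·0.9 = 35%; 1-KM = 1 − 0.1^0.39 = 59%.
- Treated: true 0.19·0.9 = 17%; 1-KM = 1 − 0.1^0.19 = 35%.

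This shows the direction of the bias. It compares the arms at equal q and not at equal time, so it should not be read as a treatment difference at a given hour.

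**4. Simulation over the protocol's 2–5 days.** Assumed: death uniform over 48–120 h in both arms and final rates of 39% and 19%. Onset of rattle is either spread evenly from recognition of the dying phase to death, or uniform over the last 24 h. Entries are true cumulative incidence / 1-KM, in per cent.

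| Arm, onset | 48 h | 72 h | 96 h | 120 h |
|---|---|---|---|---|
| Control, even | 23.9 / 23.9 | 32.9 / 34.4 | 37.6 / 42.7 | 39.0 / 49.9 |
| Control, last 24 h | 6.5 / 6.5 | 19.5 / 21.2 | 32.4 / 42.4 | 39.0 / 67.2 |
| Treated, even | 11.7 / 11.7 | 16.1 / 16.9 | 18.3 / 21.2 | 19.0 / 24.9 |
| Treated, last 24 h | 3.2 / 3.2 | 9.5 / 10.6 | 15.8 / 22.3 | 19.0 / 38.0 |

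The control-arm excess is 0 at 48 h, 1.5–1.7 points at 72 h, 5.1–10.0 at 96 h and 10.9–28.2 at the end. At the end the difference between arms on 1-KM is 49.9 − 24.9 = 25.0 points or 67.2 − 38.0 = 29.2 points, against a true 20. With 90 patients per arm and even onset, the control curve averages 34.3% at 72 h, 42.7% at 96 h and 49.2% at the end, so the pattern holds at the trial's size.

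**5. Shorter survival (assumed gamma, shape 2, mean 48 h).** With onset in the last 24 h, control is 28% true / 34% 1-KM at 48 h and 37% / 59% at 96 h; treated is 18% / 33% at 96 h. With even onset, the control excess at 96 h is about 16 points. By 96 h only about 8% are still at risk (onset in the last 24 h), roughly 7 of 90 per arm.

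**6. The log-rank test.** With 90 per arm and no effect on rattle or death, the simulated type I error is 5.4%. With equal rattle hazards and a death hazard 1.5 times higher in one arm it is 5.0%, although the crude shares then differ: 0.39/(0.39 + 0.61) = 39% and 0.39/(0.39 + 0.61·1.5) = 30%.

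**The case against.** The strongest reply is that the protocol already answers the question about proportions. The primary outcome is a crude percentage that counts each death without rattle as a non-event, and readers will have it beside any curve. This stands, and it limits the point to a secondary analysis.

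The log-rank test is also defensible. Comparing the hazard of rattle among patients still alive and free of it is a legitimate aim for a preventive drug, and step 6 shows that its error rate holds. A reader might infer that naming the log-rank test makes the comparison invalid; it does not. The limit is one of interpretation: if treatment altered time to death, equal hazards need not mean equal proportions.

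A reader might also infer that the curves are badly wrong throughout. They are not: there is no bias before the first deaths, and it is small while most patients are alive. The largest figures belong to the tail, where few remain at risk.

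Nor do the documents show that most rattle begins in the last 24 h. The Background gives rattle at least once in 40% of patients during the dying phase and in 35% during the last 24 h. That is presence of any reported rattle, not onset of grade ≥ 2 at two consecutive measurements. Onset in the last 24 h is therefore only one assumed scenario.

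Finally, the article is condensed, and a fuller plan might add competing-risk curves or keep patients who die without rattle in the risk set to the end of follow-up. The latter would make 1-KM equal the cumulative incidence. The article does not say this, and the method it names ordinarily implies censoring at death.

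**Conclusion.** The point holds for the Kaplan-Meier curves of this secondary outcome and should be fixed. If deaths are censored, 1-KM does not estimate the share of patients who rattle and overstates it increasingly over time.

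The direction follows from the design itself: follow-up to death, with most patients dying without the event. The size rests on assumed timings that the documents do not give. Over the protocol's own 2–5 days the excess in the control arm is modest to 96 h and about 10–28 points by the end. With a mean survival of 48 h it appears sooner, at about 6 points by 48 h and 16–22 points by 96 h.

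That the trial's main conclusion or its sample size is at risk is not supported: the primary percentage, its test and the totals of 180 and 200 do not depend on this analysis.

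**What to change.** In Secondary study parameters analysis, state that death without rattle is a competing event for time to death rattle. Report Aalen-Johansen cumulative incidence curves by arm in place of 1-KM, with Gray's test if the curves are to be compared. Keep the log-rank test, labelled as a comparison of cause-specific hazards of rattle.

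The cost is a sentence or two of text and slightly more analysis work. Stata, already one of the named packages, can do this. Observation to death is already planned, so no new follow-up is needed; the time of death should be confirmed as a recorded item, since the article implies it without stating it. The sample size does not change.

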#### Study

For this study, standard care procedures in the hospice facilities are extended with some extra steps:At admission: the doctor assesses if the patient meets the inclusion criteria of the study. If so, the patient is informed about the study and invited to think about participation. Written information will be given. After a period for reflection (maximum 48 h), the patient will get the opportunity for asking additional questions and, if he/she is willing to participate, to sign the informed consent form. The patient and family are aware of the fact that the study will not start immediately, but at the moment the dying phase is recognized. The doctor also informs the patient and relatives about the questionnaire which will be sent to relatives three months after the death of the patient.Start of the dying phase: the actual study (the intervention) starts with the recognition of the dying phase. The exclusion criteria will be checked again. In case of eligibility, the first dose of the study medication scopolaminebutyl 20 mg (=1 ml) or placebo (=1 ml NaCl 0.9%) will be administered subcutaneously. The study medication will be provided four times a day. The study medication is packed in numbered boxes.Care program: the CPD is extended with extra observations related to the study. The extra observations include restlessness, scored according to the Vancouver Interaction and Calmness Scale (VICS score) [20] and death rattle, scored according to Back [4]. Nurses also report on the oral care given.Relatives: three months after a patient’s death, relatives will be sent a questionnaire.

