### Measurement instruments

Table 2 provides an overview of measurement tools used in the SILENCE study.

**Table 2 Tab2:** Measurement tools

	Measurement tool
Death rattle	Scale of Back: 0 = no rattle, 1 = audible close to the patient, 2 = audible standing at the end of the bed, 3 = audible standing in the door opening [4]
Restlessness	Vancouver Interaction and Calmness Scale (VICS score): 5 questions about restlessness scored on a 6-point Likert scale [20]
Dry mouth/urinary retention	Reported observations in CPD (agreed standards, implemented for this study)
Grief	Inventory of Traumatic Grief: 30 questions about grief [21]
Quality of life	Numeric rating scale (0 = worst quality – 10 = best quality) [22]
Quality of dying	Numeric rating scale: 0 = worst quality – 10 = best quality); 15 qualitative descriptions (peaceful, quiet, shocking, painful, etc.) [22] to tick.

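### The 30-item grief inventory gets a chi-squared trend test and the repeated restlessness scores a one-value-per-patient test; both are valid, but numeric, hospice-adjusted analyses would use the same data better

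*Protocol article*

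**What the plan says.** **Restlessness.** Under Regular hospice care, nurses assess symptoms in the Care Program for the Dying (CPD) every four hours until death, and the dying phase is put at 2-5 days. Under Study, the CPD is enlarged: "The extra observations include restlessness, scored according to the Vancouver Interaction and Calmness Scale". Table 2 describes this scale (VICS) as five items on a 6-point Likert scale. The analysis section then states: "Restlessness will be compared using the t-test or, if necessary, the Mann-Whitney U-test". It names no per-patient value.

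**Grief.** Table 2 lists "Inventory of Traumatic Grief: 30 questions about grief" (the ITG). Relatives receive it once, three months after the death. In the analysis section the ITG shares a sentence with relatives' experience of the trial. Both are to be described and "compared using the Chi squared test for trends". No ordered categories are given.

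**Neighbouring scales.** In the same paragraph, the 0-10 ratings of quality of life and quality of dying get a t-test, or Mann-Whitney U if needed.

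**Hospice.** Randomization is stratified by centre. None of these secondary comparisons uses that stratification.

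**The concern.** A chi-squared test for trend is normally applied to a few ordered groups. Naming it for a 30-item inventory invites cutting the score, and cutting loses power. It is also inconsistent that an 11-point rating gets a test for numeric data while a much finer score gets one for ordered categories.

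For restlessness, a two-sample t-test or Mann-Whitney U takes one independent value per patient, whereas the record appears to supply many correlated values, in unequal number. How well the test uses them depends on what is fed into it: a patient mean uses every score, a single score discards the rest, and pooling would treat repeats as independent.

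At stake are the precision of one of three named harms and of the only bereavement comparison. Both are secondary.

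**Working it through.** **1. The plan's own figure.** The only sample-size figure concerns the primary outcome: "We aim to reduce the occurrence of death rattle from 39 to 19" per cent, and "Given a two-sided significance level of 0.05 and 80% power, a total of 180 patients are required based on a continuity-corrected Chi-square test".
- Mean proportion 0.29. Per arm without correction: [1.96·√(2·0.29·0.71) + 0.84·√(0.39·0.61 + 0.19·0.81)]² / 0.20² ≈ 79.6, so 80.
- With continuity correction: (79.6/4)·[1 + √(1 + 4/(79.6·0.20))]² ≈ 89.3, so 90 per arm and 180 in total.
- 180/0.9 = 200, matching "200 patients are needed in total".

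Both figures reproduce. None is stated for restlessness or grief. Allocation is 1:1 ("verum and placebo are equally distributed over both patients and sites"), so 90 per arm is used below.

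**2. Scores per patient.** 2 days: 48/4 = 12. 5 days: 120/4 = 30. Four-hourly VICS scoring is inferred from the CPD schedule; the article does not state it for VICS itself.

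**3. Restlessness.** With total variance 1 and within-patient correlation ρ, a mean of m scores has variance ρ + (1−ρ)/m, against 1 for a single score. At m = 20 and ρ = 0.3 the ratio is 1/(0.3 + 0.7/20) ≈ 3.0; at ρ = 0.7 it is 1/(0.7 + 0.3/20) ≈ 1.4.

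Simulation: 90 per arm, 12-30 scores per patient, number of scores unrelated to arm or score, t-test, assumed difference 0.3 SD for power.

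| ρ (assumed) | Type I error, patient mean | Type I error, pooled scores | Power, patient mean | Power, single score |
|---|---|---|---|---|
| 0.1 | 5.5% | 27% | about 100% | 52% |
| 0.3 | 4.1% | 47% | 93% | 52% |
| 0.5 | 5.6% | 55% | 79% | 52% |
| 0.7 | 5.3% | 62% | 66% | 50% |

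The pooled column is shown only to mark where the test would fail; the article does not describe that analysis.

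**4. Grief, ungrouped score.** The trend statistic is (N−1)r², where r is the correlation of score with arm; the t-test has t² = (N−2)r²/(1−r²). At N = 180 the trend test reaches 3.84 when r² = 3.84/179 = 0.0215. Then t = √(178·0.0215/0.9785) ≈ 1.98, close to its own 5% critical value of about 1.97. On the uncut score the two tests are practically the same.

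**5. Grief, score cut into quantile groups.** Simulation: roughly normal score; differences of 0.42 SD (90 per arm) and 0.64 SD (40 per arm, an assumed questionnaire return), chosen to give the t-test about 80% power.

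| Trend test on | Power, 90 per arm | Power, 40 per arm |
|---|---|---|
| Uncut score | 79% | 80% |
| 5 groups | 74% | 75% |
| 4 groups | 73% | 75% |
| 3 groups | 71% | 70% |
| 2 groups | 60% | 63% |

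The t-test had 78-81% in the same runs. Type I error of the trend test was 4.4-5.6% throughout. Cross-check: a median split of a normal score keeps 2/π = 0.64 of the information. At 80% power the expected z is 1.96 + 0.84 = 2.80; 2.80·√0.64 = 2.24, and Φ(2.24 − 1.96) ≈ 0.61, in line with the last row.

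**The case against.** The case for leaving the plan alone is substantial.

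- **Per-patient summary.** A t-test presupposes one value per patient, and the ordinary reading is a summary chosen in the full protocol or analysis plan, neither of which is shown. This stands: the unnamed summary is not by itself a fault in an article.
- **Pooling.** A reader might infer that the 4-hourly scores will enter the t-test as independent observations, with type I error of 27-62%. The documents do not support this: no section plans pooling, and a t-test on patient means keeps its error rate.
- **Misuse or loss of data.** A reader might infer that both tests necessarily misuse or throw away data. They do not. A mean uses every score, and the trend test can run on the uncut ITG score with almost no loss. No cut-points are announced.
- **Occurrence versus score.** Restlessness appears under the occurrence of adverse events but is tested as a score. That item is an umbrella heading, and the analysis section marks only urinary retention and dry mouth as yes/no. Little follows from it.
- **Relatives' experience.** The trend test suits ordered items on trial participation, which share the ITG's sentence. This stands, and is a reason to keep it there.

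What remains is the stated choice of a categorical-type test for a 30-item inventory beside numeric tests for coarser scales, and a restlessness comparison that makes no stated use of the repeated scores or the hospice strata.

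**Conclusion.** The point holds as an inexpensive improvement, not as an error that invalidates an analysis. For grief, the loss arises only if the score is cut: from about 80% power to about 73-75% with 4-5 groups, 70-71% with 3 and 60-63% with 2. For restlessness, the loss arises only if one score per patient is used: power of about 50-52%, against 66-100% with the patient mean, at a 0.3 SD difference.

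These sizes rest on assumptions that the article does not supply: the correlation range 0.1-0.7, the effect sizes, a roughly normal grief score, quantile groups, 40 returned questionnaires per arm in one setting, and four-hourly VICS scoring. An inflated false-positive rate for restlessness is not part of the conclusion. The primary analysis and the 180/200 sample size are untouched.

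**What to change.** - **Grief.** Compare the ITG total as a numeric score by linear regression on arm, adjusted for hospice, with a Wilcoxon test if the distribution is very skewed. Keep the trend test for single ordered items on relatives' experience.
- **Restlessness.** Use all VICS scores from the start of the dying phase to death, under intention-to-treat, in a mixed model with a random patient intercept, or compare per-patient means. Adjust for hospice in either case. Add the first CPD score as a covariate only if it is confirmed to precede the first dose, which the article does not state. Report the mean difference with a 95% confidence interval.

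**Cost.** Changed analysis wording and slightly more modelling, with no new data. The mixed model must acknowledge that follow-up ends at death, so the number of scores depends on survival time; the per-patient mean is simpler but gives short and long courses equal weight.
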